## Abstract

**Background:**

Trauma is a major source of morbidity and mortality, especially in people below the age of 50 years. For the evaluation of trauma patients CT scanning has gained wide acceptance in and provides detailed information on location and severity of injuries. However, CT scanning is frequently time consuming due to logistical (location of CT scanner elsewhere in the hospital) and technical issues. An innovative and unique infrastructural change has been made in the AMC in which the CT scanner is transported to the patient instead of the patient to the CT scanner. As a consequence, early shockroom CT scanning provides an all-inclusive multifocal diagnostic modality that can detect (potentially life-threatening) injuries in an earlier stage, so that therapy can be directed based on these findings.

**Methods/design:**

The REACT-trial is a prospective, randomized trial, comparing two Dutch level-1 trauma centers, respectively the VUmc and AMC, with the only difference being the location of the CT scanner (respectively in the Radiology Department and in the shockroom). All trauma patients that are transported to the AMC or VUmc shockroom according to the current prehospital triage system are included. Patients younger than 16 years of age and patients who die during transport are excluded. Randomization will be performed prehospitally.

Study parameters are the number of days outside the hospital during the first year following the trauma (primary outcome), general health at 6 and 12 months post trauma, mortality and morbidity, and various time intervals during initial evaluation. In addition a cost-effectiveness analysis of this shockroom concept will be performed.

Regarding primary outcome it is estimated that the common standard deviation of days spent outside of the hospital during the first year following trauma is a total of 12 days. To detect an overall difference of 2 days within the first year between the two strategies, 562 patients per group are needed. (alpha 0.95 and beta 0.80).

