## Methods/design

### Study objectives

The primary objective is to prove the beneficial effects of early shockroom CT scanning on trauma patients by comparing the effects of a strategy involving early shockroom CT scanning with a standard diagnostic imaging strategy on patient outcome. In the latter strategy the CT scan is not located in the shockroom, but elsewhere in the hospital. The secondary objectives are to document the impact of introducing shockroom CT-scanning on logistics, capacity utilization, waiting times, economies of scale, substitution patterns, and investments.

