### Study design

The REACT-trial is a prospective, patient-randomized study that will compare the clinical work-up of trauma patients in a setting where the CT scanner is located in the shockroom (AMC) with the standard situation where CT scanning takes place at the Radiology Department (VUmc).

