### Setting/Participating centers

The Trauma Center North-West Netherlands is one of 10 designated Level-I trauma centers in the Netherlands. It is constituted by the 'Vrije Universiteit' medical center (VUmc) and the Academic Medical Center (AMC), which are both located approximately 8 kilometers apart from each other in Amsterdam. Each of these two hospitals, together with the surrounding affiliated hospitals, is responsible for the care of trauma victims in its region (2.7 million inhabitants in total) that are distributed over these hospitals. In both hospitals, patients are evaluated by a multidisciplinary team in the trauma resuscitation room ('shockroom'), which is fully equipped for initial management of trauma patients, including conventional X-rays and ultrasonography.

The initial evaluation of trauma patients after arrival is according to ATLS guidelines and the same in both hospitals. After the primary survey, standard X-rays (i.e. thorax, pelvis and cervical spine) and sonography will be done according to the ATLS guidelines.

In the VUmc the CT scanner (64-slice) is located in the Radiology Department on the second floor. This requires transportation of the patient with at least 4 patient transfers from trolley to the CT table and vice versa.

In the AMC a concept was developed in which the CT scanner is transported to the patient instead of the patient to the CT scanner. Main feature is a radiolucent trauma resuscitation table and a 4-slice CT scanner (SOMATOTOM Sensation 4, Siemens) placed on a rail which enables the scanner to slide over the patient. Because of a mirrored design of a second shockroom that is separated by radiation shielded sliding doors the CT scanner can be transferred over the rails into the second room after the imaging is finished. The first advantage of this design is that no interference is experienced from the CT scanner during trauma resuscitation. Secondly, the design allows simultaneous use of the mirrored trauma rooms, with the sliding CT scanner accessible to both rooms.

Both trauma resuscitating settings are equipped with a conventional X-ray installation and ultrasound. As a result of the AMC concept no further patient transport or transfers are necessary for obtaining a CT scan and all radiography can be performed in the trauma room. In addition, at any time during trauma resuscitation CT imaging can be performed.

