Because of the additional CT scanning capacity that was created by adding the sliding CT scanner that services the two mirrored trauma rooms, logistics for the radiology department will be influenced for both acute (trauma) patients and elective CT scanning. By potentially eliminating the need to reckon with unplanned acute CT imaging, the regular elective CT scans can be planned better and more efficient, possibly leading to a reduction of waiting times and waiting lists. Critically ill patient groups (i.e. trauma patients and patients with intracranial bleedings, acute aneurysms or abdomens, ICU patients, etc.) who need CT scanning can have their total diagnostic work-up completed in the shockroom before transport to their destination of treatment. In some cases the diagnostic work-up can even be completed simultaneously for two patients because of the mirrored shockroom design.

Furthermore, the REACT study design enables us to describe in detail the diagnostic and therapeutic procedures following initial CT scanning of trauma patients in the shockroom or at the Radiology Department. We may be able to demonstrate a trade-off in the volume and cost of health care use between early detection of injuries and timely therapeutic management on one hand and late detection by additional diagnostic testing and subsequent therapies on the other.

Another possible institutional effect might be that a shockroom CT scan may be used as an attractive alternative to other imaging procedures or to sequential diagnostic testing strategies in other patient groups (for instance stroke patients, patients with acute abdominal pain, etc), since it remains an all-inclusive multifocal diagnostic modality. As a consequence substitution of diagnostic modalities or changes in patient groups presenting for CT scanning may occur as a result of joint production.

Finally, the total costs of realizing this concept are of substantial amount and therefore this shockroom design has to be assessed during the study period in a cost-effectiveness analysis.

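### CT location and hospital are the same variable, and the two scanners differ, so the trial compares two hospital workflows and cannot attribute a result to CT location alone

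*Protocol article*

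**What the plan says.** The abstract of the Protocol article (Methods/design) describes a randomized comparison of two level-1 trauma centers, "with the only difference being the location of the CT scanner". Study objectives states the aim in causal terms: "The primary objective is to prove the beneficial effects of early shockroom CT scanning on trauma patients". Study design places the shockroom scanner at the AMC and the Radiology Department scanner at the VUmc, one hospital per arm.

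Setting/Participating centers then describes the equipment. For the control hospital: "In the VUmc the CT scanner (64-slice) is located in the Radiology Department on the second floor". For the intervention hospital: "a 4-slice CT scanner (SOMATOTOM Sensation 4, Siemens) placed on a rail which enables the scanner to slide over the patient". The same section describes a mirrored second shockroom at the AMC, where "the design allows simultaneous use of the mirrored trauma rooms, with the sliding CT scanner accessible to both rooms", and the Discussion refers to extra capacity there: "Because of the additional CT scanning capacity that was created by adding the sliding CT scanner".

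On what the hospitals share, the section says that initial evaluation follows ATLS in both and that both shockrooms have X-ray and ultrasound. It does not say that care after the initial evaluation is the same. Data analysis adjusts for gender, mechanism of trauma, GCS, RTS and intubation, and describes the final comparison as one between the two hospitals.

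**The concern.** The abstract asserts a property that the design needs for its causal claim and that the body of the article shows it lacks. The item that differs is the CT scanner itself, the device under study.

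Even with identical scanners, one hospital per arm would leave CT location inseparable from anything else tied to the hospital. The primary outcome, days outside the hospital in the first year, depends by the article's own account (Endpoints) on mortality, length of the initial stay and readmission. Those reflect a patient's whole course, not only the first hour in the shockroom. At stake is the interpretation of the primary result. A significant difference would be read as proof that shockroom CT helps, and a null result as evidence that it does not, when the data could support neither statement about location as such.

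**Working it through.** **Inputs.** From Sample size: SD 12 days, target difference 2 days, two-sided significance level 0.05, power 0.80, 562 per group. From Study design: one hospital per arm. From Setting/Participating centers: 64-slice and 4-slice scanners.

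**The plan's own figure.** n per group = 2 × [12 × (1.96 + 0.84) / 2]² = 2 × 16.8² = 564.5. An exact calculation gives 566. Power at 562 per group is 79.8%. The stated 562 is reproduced closely enough, and the sample size is not in dispute.

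**The passages side by side.** The abstract allows one difference between the centers, scanner location. The setting section gives a second, scanner type. The mirrored room and added capacity are further differences, but they can fairly be counted as part of the AMC concept being tested. Slice count is the documented difference that lies outside it.

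**What can be estimated.** Let θ be the effect of CT location and h the effect of everything else that differs between the hospitals. The difference in means between patients allocated to the AMC and to the VUmc estimates θ + h. Location and hospital take the same value for every allocated patient, so no analysis of these data separates θ from h. More patients in the same two hospitals would estimate the sum more precisely and leave the split unknown. The covariates in Data analysis describe the patient, so adjusting for them does not remove h.

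**Illustration.** The values of h below are assumptions, since the documents give none.

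- SE of the difference = 12 × √(2/562) = 0.716 days.
- With θ = 0, the probability of a significant result is 1 − Φ(1.96 − h/SE) + Φ(−1.96 − h/SE).

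| Assumed h (days) | h/SE | Probability of p < 0.05 with θ = 0 |
|---|---|---|
| 0 | 0 | 5% |
| 0.5 | 0.70 | 10.7% |
| 1 | 1.40 | 28.7% |
| 1.5 | 2.10 | 55.4% |
| 2 | 2.79 | 79.8% |

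The last row matches the planned power, as it must: a hospital difference as large as the target effect is detected as readily as the target effect. A difference of opposite sign to a real location effect would hide it in the same way.

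**The case against.** The strongest reply is that most of the article already frames the comparison as one of strategies. The phrase about a single difference stands only in the abstract. Study design compares settings, the Discussion speaks of the Amsterdam Trauma Workflow concept, Data analysis compares the two hospitals, and both slice counts are reported openly. The sliding scanner is presented as unique to the AMC, so several hospitals per arm was hardly an option. Initial evaluation is stated to be the same in both places, and the two hospitals together form one designated trauma center. All of this is fair. It makes the needed correction smaller, but it leaves the abstract's false statement and the objective's causal wording in place, and shared initial evaluation says nothing about later care.

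A reader might be tempted to go further in four ways that the documents do not support.

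- *The planned test is invalid or its confidence interval too narrow.* The patient-level test is valid for allocation to the AMC versus the VUmc. The difficulty is attribution, not a missing variance term.
- *Surgical or ICU teams, discharge or transfer practice differ.* Nothing in the article says so. Such differences are possible, and their equality is not stated either.
- *The 64-slice scanner is faster and therefore favors the control arm.* The article gives slice counts, not scan times. The direction of any bias is unknown.
- *Every allocated patient reaches the allocated hospital.* Randomization lets ambulance staff waive the outcome in extreme cases, so the identity of arm and hospital holds for allocation, which is the basis of the main analysis.

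**Conclusion.** The point stands in a limited form. The abstract's statement that location is the only difference is wrong on the article's own facts, and with one hospital per arm the trial cannot isolate the effect of CT location. It can validly compare the two hospitals' workflows as whole packages. The defect governs what may be concluded from the primary result, so the wording should be corrected; the sample size and the planned test can stay as they are.

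The contradiction and the confounding rest on the text alone. The error rates of about 11%, 29% and 80% rest on assumed hospital differences of 0.5, 1 and 2 days and on the planned SD being right. They show how sensitive the attribution would be, and are not estimates of what happened or will happen in this trial.

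**What to change.** Three changes of wording:

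1. In the abstract, delete the phrase that makes CT location the only difference between the centers.
2. Restate the primary objective (Study objectives) and the concluding statements (the abstract's Discussion and the Conclusion) as the effect of allocation to the AMC shockroom-CT workflow versus the VUmc radiology-CT workflow.
3. State as limitations that the scanners differ (4-slice and 64-slice) and that each arm is a single hospital, so that neither a difference nor its absence can be attributed to CT location alone.

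Subtracting a historical AMC–VUmc difference from the trial result is not recommended. The historical data mentioned under Sample size are cited for admission numbers only, so usable outcome data are not shown to exist. Each hospital also has its own region, so a historical difference would mix case mix with hospital effect and carry that confounding into a randomized comparison.

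The cost is some editing and a narrower claim. No change to conduct, sample size or analysis is needed.

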**Discussion:**

The REACT-trial will provide evidence on the effects of a strategy involving early shockroom CT scanning compared with a standard diagnostic imaging strategy in trauma patients on both patient outcome and operations research.

**Trial registration:**

ISRCTN55332315

## Background

Trauma is the most common cause of death in people younger than 50 years of age and accounts for more years of life lost than cancer, heart disease, and stroke combined. Injuries cause 5 million deaths every year worldwide (9% of global mortality).[1] In Europe alone injuries account for approximately 800,000 deaths (10% of all deaths) and 14% of all disability-adjusted life years (DALY).[2] Injuries are an important source of medical costs, economic losses, and immaterial losses. Trauma can therefore be regarded as a neglected epidemic.

For improving the trauma care specialized trauma centers are designated and specialized trauma care protocols, like the worldwide used ATLS^® ^guidelines, were developed.[3] Because there is a narrow window of opportunity between the moment that a patient deteriorates and actually dies, the ATLS guidelines prioritize care and focus on (potentially) life-threatening injuries rather than distracting but less important injuries. As a consequence a systematic approach of clinical examination and diagnostics is developed to recognize the most life-threatening injuries first. These should be treated immediately and preferably within 'the golden hour'.[3]

The imaging studies most frequently used in trauma patients include conventional X-rays, ultrasonography (FAST), and computed tomography scanning (CT). Although conventional X-rays and ultrasonography are widely used and easily accessible for many institutions, they have a limited sensitivity for injuries such as spine fractures,[4] pulmonary contusion, rib fractures, pneumothoraces or vascular injuries to the mediastinum, [5-8] and intra-abdominal, pelvic and retroperitoneal injuries.[9,10] Also, the amount of time necessary to obtain an overview of all the injuries is limited.

Recent improvements in CT technology with respect to image quality and speed have led to an increasingly important role of CT scanning in management of severely injured patients. However, the biggest problem with CT scanning is that this technique is frequently time-consuming due to logistical (location of CT scanner in other departments of the hospital) and technical issues. This implies that CT can only be used in hemodynamically stable patients where time to OR for surgical stabilization is a less critical factor. Furthermore, the fact that the same CT scanner is scheduled for elective patients as well as trauma patients means that an unplanned, prioritized trauma patient will disrupt the scheduled patient care and logistics and will lead to increased waiting times.

In order to improve patient care and workflow in acute trauma patients, the Academic Medical Center (AMC) in Amsterdam, the Netherlands, has initiated a project together with Siemens Inc. A new and revolutionary concept was developed in which the CT scanner is transported to the patient instead of the patient to the CT scanner. Main feature is a radiolucent trauma resuscitation table and a CT scanner that slides over the patient in the trauma resuscitating room. In addition there are also possibilities for conventional X-ray imaging and ultrasonography. With this concept the most important diagnostic modalities for trauma evaluation are available in the shockroom and CT scanning is possible at any moment during initial trauma evaluation. Furthermore, no further transport and patient transfers are required which can endanger the patient itself during the diagnostic phase (potentially leading to dislodgement of tubes, lines, cables, etc). Overall this concept will likely result in a faster and improved workflow and diagnostic imaging of trauma patients.

## Methods/design

### Study objectives

The primary objective is to prove the beneficial effects of early shockroom CT scanning on trauma patients by comparing the effects of a strategy involving early shockroom CT scanning with a standard diagnostic imaging strategy on patient outcome. In the latter strategy the CT scan is not located in the shockroom, but elsewhere in the hospital. The secondary objectives are to document the impact of introducing shockroom CT-scanning on logistics, capacity utilization, waiting times, economies of scale, substitution patterns, and investments.

### Study design

The REACT-trial is a prospective, patient-randomized study that will compare the clinical work-up of trauma patients in a setting where the CT scanner is located in the shockroom (AMC) with the standard situation where CT scanning takes place at the Radiology Department (VUmc).

### Setting/Participating centers

The Trauma Center North-West Netherlands is one of 10 designated Level-I trauma centers in the Netherlands. It is constituted by the 'Vrije Universiteit' medical center (VUmc) and the Academic Medical Center (AMC), which are both located approximately 8 kilometers apart from each other in Amsterdam. Each of these two hospitals, together with the surrounding affiliated hospitals, is responsible for the care of trauma victims in its region (2.7 million inhabitants in total) that are distributed over these hospitals. In both hospitals, patients are evaluated by a multidisciplinary team in the trauma resuscitation room ('shockroom'), which is fully equipped for initial management of trauma patients, including conventional X-rays and ultrasonography.

The initial evaluation of trauma patients after arrival is according to ATLS guidelines and the same in both hospitals. After the primary survey, standard X-rays (i.e. thorax, pelvis and cervical spine) and sonography will be done according to the ATLS guidelines.

In the VUmc the CT scanner (64-slice) is located in the Radiology Department on the second floor. This requires transportation of the patient with at least 4 patient transfers from trolley to the CT table and vice versa.

In the AMC a concept was developed in which the CT scanner is transported to the patient instead of the patient to the CT scanner. Main feature is a radiolucent trauma resuscitation table and a 4-slice CT scanner (SOMATOTOM Sensation 4, Siemens) placed on a rail which enables the scanner to slide over the patient. Because of a mirrored design of a second shockroom that is separated by radiation shielded sliding doors the CT scanner can be transferred over the rails into the second room after the imaging is finished. The first advantage of this design is that no interference is experienced from the CT scanner during trauma resuscitation. Secondly, the design allows simultaneous use of the mirrored trauma rooms, with the sliding CT scanner accessible to both rooms.

Both trauma resuscitating settings are equipped with a conventional X-ray installation and ultrasound. As a result of the AMC concept no further patient transport or transfers are necessary for obtaining a CT scan and all radiography can be performed in the trauma room. In addition, at any time during trauma resuscitation CT imaging can be performed.

### Endpoints

The primary outcome criterion used is the number of days spent outside the hospital in the first year following the trauma. This outcome is responsive to differences in mortality (no additional days outside hospital), to differences in hospital stay for the initial admission and to differences in readmission rate.

The secondary outcome parameters include general health outcome at 6 and 12 months after the shockroom admission (using the EuroQol and HUI-3 questionnaires), morbidity and mortality during the first year following the trauma and various time intervals and process of care parameters of the initial admission (time to intervention, time to active bleed management, ICU and total hospital stay, etc.). Furthermore the radiation dosage is calculated in both strategies based on the actual number and type of radiological examinations related to the initial trauma performed in each patient during the first year.

